Several methods have been used to reduce acute adverse reactions to antivenom. A small test dose of antivenom to detect patients who may develop acute adverse reactions to the antivenom has no predictive value, can itself give rise to anaphylaxis, and is no longer recommended [Malasit et al., 1986]. Prophylactic use of hydrocortisone and antihistamines before infusion with antivenom is also practised widely, although the theoretical basis for their use is unclear. Antihistamines counter only the effects of histamine after its release and do not prevent further release, and one small randomised controlled trial demonstrated no benefit from the routine use of antihistamines [Fan et al., 1999]. Hydrocortisone takes time to act and may be ineffective as a prophylactic against acute adverse reactions that can develop almost immediately after antivenom treatment, which is very often administered urgently to snakebite victims. A recent study suggests that intravenous hydrocortisone is ineffective in preventing acute adverse reactions to antivenom, but if given together with intravenous chlorpheniramine (an antihistamine) it may reduce these reactions [Gawarammana et al., 2004]. However, this trial recruited only 52 patients and was not designed to study the efficacy of chlorpheniramine alone, making clear interpretation of the results and recommendations on pretreatment with steroids and antihistamines to prevent acute reactions to antivenom difficult.

In one study of 105 patients low-dose adrenaline given subcutaneously immediately before administration of antivenom to snakebite victims significantly reduced the incidence of acute adverse reactions to the serum [Premawardena et al., 1999]. However, the authors were unable to enrol sufficient participants to adequately establish safety, a major concern regarding the use of adrenaline in a prophylactic role [Khanna & Hawkins, 1999], particularly the risk of intra-cerebral haemorrhage [Dassanayake et al., 2002; Horowitz et al. 1996]. Therefore, further studies on the safety of this treatment are required before it can be recommended routinely.

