# TRIAL DESIGN

**Objective**

To determine whether low-dose adrenaline, promethazine, and hydrocortisone, alone and in different combinations, are significantly better than placebo in the prevention of acute adverse reactions to antivenom in snakebite victims. The principle outcomes will be the development of acute reactions to antivenom. This study also aims to assess the safety of pretreatment medication used before the administration of antivenom.

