**Secondary outcomes:**

Comparisons will be made of the effects of each of the study treatment allocations on rates of severe reactions at first 1 or 6 hrs, rates of any adverse reactions (mild, moderate, and severe) in the first 48 hrs, and acute adverse reactions to study treatments separately.

Classification of adverse reactions:Tertiary (Brown, 2004):

- Mild – fever, rigors, pruritus, urticaria, facial oedema
- Moderate – bronchospasm, stridor, abdominal pain, nausea, vomiting
- Severe – hypotension SBP below 80 mmHg, cyanosis, confusion, altered or loss of consciousness

Specified adverse reactions to study treatments

- Development of arrhythmias, ischaemic changes on the ECG after the trial drug and antivenom
- A significant rise in blood pressure (systolic > 30 mmHg or diastolic) after the trial drug and antivenom
- Intracerebral haemorrhage

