**DATA ANALYSIS**

# Methods of analysis

The fundamental assessments of efficacy will involve comparisons of the proportions of patients experiencing an event among all the randomised patients in their originally allocated treatment group, irrespective of what treatment they were actually given (i.e. “intention-to-treat” analyses). Two-sided P values will be used. No allowance will be made for multiple hypothesis testing in the primary comparison of each of the three study treatments in this 2 x 2 x 2 factorial study. For secondary and, particularly, for tertiary comparisons, allowance will be made for multiple hypothesis testing, taking into account the nature of the events (including timing, duration, and severity) and evidence from other studies.

The independent effects and effects of interactions of the three interventions will be assessed by using Cox regression. Cox regression will be used with a constant time to event for all subjects as we are only interested in reaction rate and not in the time to reaction.

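### The multiplicity allowance for secondary comparisons also covers the drug-harm comparisons, where it can only make a real harm harder to declare

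*Protocol*

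**What the plan says.** Safety is an aim of the trial. The Synopsis names it beside efficacy, and the Objective says: "This study also aims to assess the safety of pretreatment medication used before the administration of antivenom". Part of the reason is given in Background to the Study, which says of the 105-patient adrenaline study that "the authors were unable to enrol sufficient participants to adequately establish safety, a major concern regarding the use of adrenaline in a prophylactic role", and singles out bleeding into the brain as the risk of most concern.

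Secondary outcomes puts the drug harms among the comparisons by allocation. The sentence begins "Comparisons will be made of the effects of each of the study treatment allocations on rates of severe reactions at first 1 or 6 hrs" and ends "and acute adverse reactions to study treatments separately". The list of specified reactions to study treatments that follows covers arrhythmia and ischaemic ECG changes, a rise in blood pressure, and "Intracerebral haemorrhage".

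Methods of analysis sets the testing rule: "Two-sided P values will be used". The primary comparison of each of the three drugs gets no allowance for multiple testing. Then: "For secondary and, particularly, for tertiary comparisons, allowance will be made for multiple hypothesis testing". The sentence goes on to say that the allowance will weigh what kind of events they are, their timing, duration and severity, and outside evidence. It names no method and no numerical level, and makes no exception for harms.

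**The concern.** A multiplicity allowance protects against declaring an effect that is not there. That suits secondary claims of benefit. For a harm, the error that matters more is failing to declare an effect that is there, and any allowance makes that error more likely. As written, the plan applies the safeguard to harm and waives it for the primary tests of benefit.

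What is at stake is how clearly the trial can answer its safety question. Background to the Study says more safety evidence is needed before prophylactic adrenaline can be routinely recommended. If an excess of a serious event is discounted for multiplicity, that evidence is weakened by a rule that has no purpose there. An analysis plan written to follow this protocol would inherit the rule.

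**Working it through.** **1. Which rule reaches the harm comparisons.** Secondary outcomes lists reactions to study treatments as a comparison by allocation. Methods of analysis applies the allowance to secondary comparisons and, more strongly, to tertiary ones. The word Tertiary appears in the classification line above the list of specified reactions; if that list were read as tertiary, the allowance would apply all the more. Neither reading exempts harms.

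**2. The plan's own figures.** The Protocol gives no power, precision or expected rate for harms. Its only power figures (Sample size and predicted events) concern antivenom reactions. For 40% v 30% with 500 v 500 at two-sided 0.01, the normal approximation gives

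Φ[(0.10 − 2.576 × √(2 × 0.35 × 0.65/500)) / √((0.24 + 0.21)/500)] = Φ[(0.10 − 0.0777)/0.0300] = Φ(0.743) = 77.1%,

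against a stated 80%. This is a small, separate discrepancy and does not bear on the present point.

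**3. Inputs for the illustration.** Group sizes of 500 v 500 come from the power table, and the two-sided test from Methods of analysis. Assumed: all harm rates, the Fisher exact test, the 0.05 baseline, and the stricter levels. The level 0.01 is borrowed from the sample size section; 0.05/9 would be Bonferroni over 3 drugs × 3 types of harm. The Protocol prescribes neither for harms.

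**4. Power.** Sum Bin(x; 500, p₁) × Bin(y; 500, p₂) over all pairs with y > x and Fisher P below the level.

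| No drug v drug (assumed) | 0.05 | 0.01 | 0.05/9 |
|---|---|---|---|
| 0 v 0.5% | 4.2% | 0.4% | 0.1% |
| 0 v 1% | 38.4% | 13.2% | 6.7% |
| 1% v 2% | 17.9% | 5.5% | 3.5% |
| 1% v 3% | 56.1% | 30.1% | 22.9% |
| 2% v 4% | 39.9% | 18.9% | 13.6% |
| 5% v 10% | 83.2% | 63.5% | 55.4% |

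**5. Check by hand.** With no events in one group and y in the other, Fisher P = 2 × C(500, y)/C(1000, y).
- y = 5: 2 × (500/1000 × 499/999 × 498/998 × 497/997 × 496/996) = 0.062.
- y = 6: 0.062 × 495/995 = 0.031.
- y = 8: 0.0076.
- y = 9: 0.0038.

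So against none, significance needs 6 events at 0.05, 8 at 0.01 and 9 at 0.05/9. The 0 v 1% row is the chance that a Bin(500, 0.01) count reaches 6, 8 or 9.

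**6. Separating size from allowance.** For 0 v 1%, 100 − 38.4 = 61.6% of such trials miss the harm at 0.05 with no allowance at all. That is the limit of 1000 patients. The allowance accounts only for the further fall: 38.4 − 13.2 = 25.2 points at 0.01, or 38.4 − 6.7 = 31.7 points at 0.05/9. For 5% v 10% the falls are 83.2 − 63.5 = 19.7 and 83.2 − 55.4 = 27.8 points.

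**7. What an interval adds.**
- Zero events in 500: the exact upper limit of the two-sided 95% interval is 1 − 0.025^(1/500) = 0.74%.
- 0 v 0: the Newcombe 95% interval for the risk difference runs to 0.76 points either way.
- 0 v 5: the risk difference is 1.0 point, Newcombe interval 0.05 to 2.3 points, beside Fisher P = 0.062. The two methods fall on opposite sides of significance here, so the interval method for rare events should be named in advance.

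**The case against.** The strongest reply is that the allowance is not a mechanical threshold. The same sentence ties it to the nature and severity of the events and to outside evidence. A sensible reader could therefore make little or no allowance for intracerebral haemorrhage, about which the Background already cites outside concern. This stands: the size of the effect cannot be fixed, and the stricter levels above are illustrations. It also cannot be said that harms face a numerically stricter level than efficacy, because Methods of analysis fixes no level for either and the trial was sized at 0.01. The direction still holds. An allowance can be set at nothing, but it can never make a harm easier to declare.

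A reader might also infer three stronger things, none of which the document supports.

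- **That non-significance will be taken as safety.** No section says so. The Objective speaks of assessing safety, not of establishing it.
- **That P values are the only judgement of safety.** The methods paragraph opens with efficacy. Under Adverse events, serious events get immediate blinded review by the steering committee, and confirmed reports go unblinded to the chairman of the Data Monitoring Committee. That is monitoring during the trial and does not settle how the final drug v no-drug comparison is read, but safety does not rest on a test alone.
- **That the lack of a margin, upper bound or interval is itself an error.** These are commonly left to an analysis plan, and one may exist that is not shown here.

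It is also fair to say that the fix does not cure low power for rare events, since it leaves the sample size unchanged.

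**Conclusion.** The point holds in a limited form. The Protocol extends a multiplicity allowance to the comparisons of drug harms without exception and gives none to the primary efficacy comparisons, in a trial whose aims include safety. This is a rule the text states, not a gap that an analysis plan following it would fill.

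Its size is indeterminate because the allowance is qualitative. Under the assumed rates and levels, tightening from 0.05 to 0.01 or 0.05/9 costs roughly 20 to 32 points of power in the 0 v 1% and 5% v 10% cases. The loss in points is smaller where power at 0.05 is already very low, as for 0 v 0.5%. This is a wording fault that is cheap to correct; it does not undermine the design.

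**What to change.** In Methods of analysis, state that the allowance does not apply to the specified adverse reactions to study treatments or to serious adverse events. Serious adverse events are not named as a secondary comparison, but including them removes doubt. Add that each drug v no-drug harm comparison will be reported as a risk difference with an unadjusted 95% confidence interval, by a named exact method where events are rare, and that a non-significant P value will not be taken as evidence of safety.

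Optionally, add to Sample size and predicted events what the trial can exclude: no events among 500 patients allocated a drug would exclude a rate above about 0.74% in that group.

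The cost is two or three sentences, with no extra patients or data. The downside is more chance signals among the harm comparisons, which then have to be weighed on severity, plausibility and outside evidence, as the Protocol already intends.

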**Sample size and predicted events**

We estimate that acute adverse reactions occur in about 40% of patients who receive antivenom. Therefore, proportional reductions of 25-40% of acute adverse reactions would correspond to substantial absolute benefits (see Table). For an anticipated 25% reduction in adverse reactions from the current reaction rate by any one treatment with 80% power at p<0.01 using the proposed design, a sample size of 1000 would be needed for this study.

During the trial it is intended that blinded event rates (i.e. active and placebo groups combined) will be monitored and, if they are substantially lower than anticipated, the TSC will have the option of increasing the sample size.

**Table: Statistical power to detect 25-40% proportional reductions in acute adverse reactions to antivenom among 1000 randomised patients (based on 40% control group event rate)**

| **Proportional**  **reduction** | **Control group**  **500** | **Treatment group**  **500** | **Power for a type I error <0.01** | **Power for a type I error <0.05** | **Events avoided per 1000 treated** |
| --- | --- | --- | --- | --- | --- |
| 40% | 200 | 120 | >95% | >99% | 80 |
| 30% | 200 | 140 | 95% | >95% | 60 |
| 25% | 200 | 150 | 80% | >90% | 50 |

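### Constant-time Cox regression for the drug effects and interactions gives, depending on the tie rule, either a risk ratio with too wide an interval or a ratio that is not the risk ratio

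*Protocol*

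**What the plan says.** The Methods of analysis section of the protocol names two analyses. The first is by intention to treat: "The fundamental assessments of efficacy will involve comparisons of the proportions of patients experiencing an event among all the randomised patients". The second is a model: "The independent effects and effects of interactions of the three interventions will be assessed by using Cox regression". The section then describes that model: "Cox regression will be used with a constant time to event for all subjects as we are only interested in reaction rate". It also says "Two-sided P values will be used". It gives neither a rule for tied events nor a variance estimator for the Cox model.

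The planning figures are in Sample size and predicted events. The control rate is for any acute reaction: "We estimate that acute adverse reactions occur in about 40% of patients who receive antivenom". The target is "For an anticipated 25% reduction in adverse reactions from the current reaction rate by any one treatment with 80% power at p<0.01", for which "a sample size of 1000 would be needed for this study". The matching row of the power table, with 500 patients per group, reads "25% | 200 | 150 | 80% | >90% | 50".

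Under Assessment of outcome, the primary outcome is severe reactions within 48 hours. Reactions of any grade within 48 hours are secondary. No planning rate is given for severe reactions.

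**The concern.** Cox regression draws its information from the order of event times. If all times are one constant there is no order, and the fit depends wholly on how the software treats ties. Under the Breslow rule the partial likelihood becomes a Poisson likelihood. Its estimate is the ratio of reaction proportions, but its model-based variance treats each event count as Poisson and leaves out the binomial factor (1 − p). That factor is close to 1 for rare events and well below 1 at a 40% reaction rate. Under the Efron rule the estimate moves away from the ratio of proportions, although the protocol says that the reaction rate is the only interest.

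At stake are the confidence intervals and P values for the drug effects in the model, and above all for the interactions, which the protocol assigns to this model alone. The Treatment plan section pools patients on each drug regardless of the other two, so an interaction that goes undetected weakens the reading of the pooled comparisons. The model and the direct comparison of proportions could also give clearly different P values for the same contrast.

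**Working it through.** **Inputs.** From the 25% row of the power table: 500 v 500 patients, 200 v 150 events, so p0 = 0.40, p1 = 0.30, risk ratio 0.75 and log ratio −0.2877. Two-sided tests; the critical value at 0.01 is 2.576.

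**The protocol's own power figure.** A two-sided test of two proportions at 0.01 has 77.1% power, against the stated 80%; 80% would need about 1060 patients. At 0.05 the power is 91.3%, which agrees with the stated >90%. The reference below is the Wald test of the log risk ratio with binomial variance, which has 76.1% power at 0.01.

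**Breslow ties, model-based variance.**
- Cox variance of the log ratio: 1/200 + 1/150 = 0.01167; SE 0.1080; z = 0.2877/0.1080 = 2.66; P = 0.0077.
- Binomial variance: 0.60/200 + 0.70/150 = 0.00767; SE 0.0876; z = 0.2877/0.0876 = 3.29; P = 0.0010.
- Ratio of standard errors: 0.1080/0.0876 = 1.23, so the Cox SE is 23% too wide.
- Power at 0.01, taken as Φ(z − 2.576): 53.5% for Cox and 76.1% for binomial. In a simulation of 20,000 trials the figures were 54.5% and 76.6%, and 77.1% for the chi-square test.
- Power at 0.05: 75.9% v 90.8%.
- Type I error of a nominal 0.01 test when both rates are 40%: about 0.0009, by formula and by simulation.

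A fitted Cox model with Breslow ties on these counts gives ratio 0.750 and SE 0.1080, which confirms the formula.

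**Other tie rules, same data.**

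| Analysis | Estimate | z | Power at 0.01 |
| --- | --- | --- | --- |
| Cox, Breslow, model-based SE | 0.750 | 2.66 | 53.5% |
| Cox, Efron, model-based SE | 0.702 | 3.27 | 75.7% |
| Risk ratio, binomial SE | 0.750 | 3.29 | 76.1% |
| Logistic regression (odds ratio) | 0.643 | 3.31 | 76.7% |

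The Efron estimate is close to a ratio of cumulative hazards, ln(0.70)/ln(0.60) = 0.698. Its simulated type I error at nominal 0.01 is 0.0106, so it is sound as a test; what it estimates is not the ratio of reaction rates.

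**Interaction (illustration; the rates are an assumption).** Take two drugs with 250 patients per cell and reaction rates of 40%, 40%, 40% and 24%. Events are 100, 100, 100 and 60, and the interaction ratio is 0.24 × 0.40/(0.40 × 0.40) = 0.60, with log −0.511.
- Cox (Breslow): 3/100 + 1/60 = 0.0467; SE 0.216; power at 0.05 about 66%.
- Binomial: 3 × 0.60/100 + 0.76/60 = 0.0307; SE 0.175; power at 0.05 about 83%.

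**Severe reactions (control rates assumed; 25% reduction, 500 v 500, two-sided 0.01).**

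| Control rate | Breslow SE | Binomial SE | Excess | Power, Breslow v binomial |
| --- | --- | --- | --- | --- |
| 20% | 0.153 | 0.139 | 10% | 24.4% v 30.6% |
| 16% | 0.171 | 0.159 | 8% | 18.6% v 22.3% |
| 10% | 0.216 | 0.207 | 5% | 10.7% v 11.8% |
| 5% | 0.306 | 0.299 | 2% | 5.1% v 5.3% |

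The 16% row multiplies the 40% reaction rate by the Background's figure of up to 40% of cases being severe. That figure counts bronchospasm as severe, whereas the trial's own grading calls it moderate, so 16% is probably high. In simulation at 16% v 12%, power was 16.3% v 21.8%, a gap of 5.5 points where the formula gives 3.7.

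**The case against.** The strongest reply is that the power loss is conditional. It needs Breslow ties together with a model-based variance, and the protocol fixes neither. Efron ties, or a robust variance, bring power back to about 76%. Tie handling and the variance estimator are details that a protocol may leave to the statistical analysis plan, which is not at hand. This stands: the 54% figure must carry its condition, and silence on these two details is not itself the fault. It does not clear the model that the protocol does name, because neither Breslow nor Efron ties, with model-based variance, gives the risk ratio with a correct interval.

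A reader might also infer that the trial's planned power drops from about 76% to 54%. The protocol does not support that. Its main efficacy assessment compares proportions directly, the power table is for a simple comparison of two groups of 500, and such a test keeps about 77%. The loss falls on the Cox results only.

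Nor does the 40% rate describe the primary outcome. It is for any reaction, which is secondary. At the lower rates assumed for severe reactions the loss is small, and power there is low by either method. Finally, too wide an interval creates no false claims of benefit.

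**Conclusion.** The concern holds as a fault in the model chosen for the independent effects and interactions, and it is of moderate weight. At the planning rates for any reaction, Breslow ties with model-based variance make the standard error 23% too wide and give that analysis about 54% power at two-sided 0.01 instead of 76%. Efron ties keep the power but report 0.70 where the risk ratio is 0.75. For severe reactions, at control rates of 5% to 20% (an assumption, since the protocol gives none), the standard error is about 2% to 10% too wide and the loss by formula is about 0.2 to 6 points of power.

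The direct comparison of proportions is unaffected, and the error is conservative. What remains is weakened inference on interactions, a possible disagreement between two analyses of the same contrast (P = 0.0077 v 0.0010), and an estimate that depends on a software setting.

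**What to change.** Replace the Cox sentences with a regression for a binary outcome that contains the three treatment factors and their interactions. Any one of these serves, provided it is named before unblinding:

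- log-binomial regression, reporting risk ratios;
- Poisson regression, or the constant-time Cox model with Breslow ties, in either case with robust (sandwich) variance, reporting risk ratios;
- logistic regression, reporting odds ratios labelled as such.

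The change takes one sentence in the protocol or the analysis plan and a software option. It needs no further patients or data. Settling it in advance also removes a later choice between estimates of 0.75 and 0.70 from the same counts.

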# TRIAL SUPERVISION

# Trial steering committee

The Trial Steering Committee (TSC Chairman: [name] [name]) from the Faculty of Medicine, University of Kelaniya, will have overall responsibility for the trial, and will coordinate and supervise the study. They will not be directly involved with the conduct of the study or patient management / assessment. Supervisory visits to trial centres will be made by members of the TSC at regular intervals (usually once in 3-4 weeks) to monitor trial progress and ensure adherence to the trial protocol by the investigators in the trial centres. Patient CRFs will be evaluated during each visit and those that are complete will be retained for subsequent analysis.

The main function of the TSC is to maintain overall integrity of the trial. The Sri Lankan members of the TSC will meet at least once a month until the end of the trial. The UK members will be kept informed of progress after each meeting.

